## Abstract

**Background:**

Tendinopathy is a difficult problem to manage and can result in significant patient morbidity. Currently, the clinical use of platelet-rich plasma (PRP) in painful tendons is widespread but its efficacy remains controversial.

**Methods/Design:**

This study is a single-center, randomized double-blind controlled trial. Eighty patients will be allocated to have ultrasound (US)-guided needling combined with a leukocyte-depleted (that is, pure) PRP or lidocaine each alternate week for a total of two interventions. Outcome data will be collected before intervention, and at 6 weeks, 3, 6, and 12 months after intervention. Main outcome measure: Changes in pain and activity levels, as assessed by Disabilities of the Arm, Shoulder and Hand (DASH-E, Spanish version) score, at 6 months. We will compare the percentage of patients in each group that achieve a successful treatment defined as a reduction of at least 25% in the DASH-E score. Secondary outcome measures include changes in DASH-E at 3 and 12 months, changes in pain as assessed by the visual analogue scale (VAS) at the 6-week, 3-, 6-, and 12-month follow-up, changes in sonographic features and neovascularity, and percentage of patients in each group with adverse reactions at 3, 6, and 12 months.

**Discussion:**

The results of this study will provide insights into the effect of pure PRP in tendon and may contribute to identifying the best protocol for PRP application in tendinopathies.

**Trial registration:**

ClinicalTrials.gov: NCT01945528.

## Background

Tendon disorders (tendinopathies) are noteworthy in sports and occupational settings due to repetitive trauma and overuse; besides they are prevalent among individuals of all ages, and also part of the ageing process. The term ‘tendinopathy’ describes painful conditions affecting tendons associated with repetitive strain, overuse, ageing, degeneration, or poor biomechanics [1]. Tendinopathies worsen quality of life by causing pain and impairing mobility, decreasing the ability to perform daily activities, and compromising an active lifestyle.

Current research has produced several biological hypothesis based on histopathological, biochemical, and clinical findings that show cell apoptosis, angiofibroblastic features, or abnormal biochemical adaptations, largely suggesting that a failed healing response underlies the condition [2].

At present, minimally invasive interventions capable of boosting the healing response or counteracting degenerative changes in tendinopathy are being investigated. Among the emerging technologies, one investigational biological therapy, platelet-rich plasma (PRP), has been recently explored in several clinical studies [3]; in particular, several controlled clinical studies have examined the effect of PRP in epicondylitis [4-9]. PRP therapies are multitargeted approaches able to release a large pool of signals, producing an instructional biological microenvironment for local and migrating cell activities. Moreover, PRPs modulate inflammation and angiogenesis largely because of their ability to secrete high levels of growth factors and chemokines [10].

Different PRP formulations can be obtained depending on the preparation protocol, that is, single or double spinning. Most double spinning and also the buffy coat-based methods (single spinning) produce PRP with a high concentration of platelets and leukocytes relative to peripheral blood. These products are named L-PRP in contrast to pure PRP that contains a moderate concentration of platelets and absence or non-relevant concentration of leukocytes, and are generally obtained after a soft single spinning procedure [11]. The majority of clinical studies published up to now (>90%) have examined the efficacy of L-PRP injections with controversial results [12]. Assuming that leukocyte-released proteases may compromise the stability of platelet-released growth factors, better efficacy might be achieved with pure PRP injections. Currently, most published controlled studies have used corticosteroids as comparators. Instead, we propose lidocaine injections to avoid corticosteroids interference with the healing mechanisms.

We will compare the clinical outcomes and sonographic features of US-guided tenotomy combined with pure PRP with the outcome of US-guided tenotomy combined with lidocaine. This study protocol aims to evaluate the potential of pure PRP associated with needling for the treatment of epicondylitis.

## Methods/Design

### Study design

B-PRPtendon is a patient and assessor blinded superiority-type randomized controlled trial; the study will be conducted at Hospital Universitario Cruces (HUC). The research protocol is approved by the Ethics Committee of HUC and authorized by the Spanish Agency of Medicines. A total of 80 patients will be randomly allocated into one of two groups. The two groups are: US-guided percutaneous needling tenotomy combined with PRP injection each alternate week for a total of two interventions; and US-guided needling tenotomy combined with lidocaine injection each alternate week for a total of two interventions.

The study will run for 2 years. Recruitment will be for 12 months with final follow-up at 1 year post treatment (Table 1).

**Table 1 T1:** Outcome assessments

	**Study period**							
	**Enrollment**	**Allocation**	**Treatment**		**Follow-up**			
**Timepoints**	−15 days		**0**	**2 weeks**	**6 weeks**	**3 months**	**6 months**	**12 months**
Eligibility screen	X							
Informed consent	X							
Laboratory tests	X							
Allocation		X						
**Interventions**			X	X				
**Assessments**								
**DASH**			X		X	X	X	X
**VAS**			X		X	X	X	X
**Complications**			X		X	X	X	X
**Ultrasound**			X			X	X	X

### Study population

Patients will be identified, and recruited in HUC and from primary care settings of Bizkaia. Primary care physicians and research nurses will introduce the trial to the patient and refer them to an orthopedic investigator for screening and potential recruitment*.*

Patients will be treated and followed up in HUC at 6 weeks, 3, 6, and 12 months post treatment, and will be required to attend an appointment for sonographic assessments at 3, 6, and 12 months.

The inclusion criteria are: tendinopathy present in either lateral or medial elbow; patients will have failed conservative treatment; baseline elbow pain >3/10 during resisted wrist extension; history of at least two periods of elbow pain lasting >10 days; symptoms lasting at least 3 months or longer; body mass index (BMI) between 20 and 35; commitment to comply with all study procedures; and the patient must give written informed consent.

Patients may not enter the study if any of the following apply: presence of full tendon tear; BMI >35; systemic autoimmune rheumatologic disease (connective tissue diseases and systemic necrotizing vasculitis); poorly controlled diabetes mellitus (glycosylated hemoglobin above 9%); blood disorders (thrombopathy, thrombocytopenia, anemia with Hb <9); patient receiving immunosuppressive treatments; received local steroid injection within 3 months of randomization; received non-steroidal anti-inflammatory, opioids, or oral corticosteroids within 15 days before inclusion in the study; severe heart disease; patients unable to comply with scheduled visits, for work, or spend long periods away from their habitual residence; patients with active cancer or cancer diagnosed in the last 5 years; analytical diagnosis of hepatitis B, C, or HIV infection; pregnant or lactating; or people who are taking a drug in clinical investigation. Initial patient selection is conditioned to the negative results in the analytical tests for hepatitis B, C, or HIV infection.

### PRP preparation

Peripheral venous blood is collected into three 9 mL tubes containing 3.8% (wt/vol) sodium citrate. The anticoagulated blood is centrifuged at 1,200 rpm for 6 min and PRP is collected taking care to avoid contamination with the buffy coat containing the leukocytes. Plasma is kept at room temperature until intervention; the delay between blood extraction and plasma administration will not be >4 h. To avoid blood lipids in the PRP, patients will fast or follow a fat-free diet during the 6 h prior to blood extraction.

Just preceding PRP administration, 10% calcium chloride will be added, at a final concentration of 22.6 mM (50 μL per 1 mL of PRP), and the 5 mL Luer Lok syringe is filled with the activated PRP.

### Procedures

Interventions are performed by two radiologists with extensive clinical experience in musculoskeletal intervention procedures. Prior to needling and administration of PRP or lidocaine, an exploratory echography is performed to identify clefts of hypoechogenicity and/or changes in vascularity, and baseline sonographic characteristics are recorded, as described in Table 2[13].

**Table 2 T2:** Sonographic assessments

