### Randomization

Randomization will be performed in blocks of four, and equal allocation ratio will be achieved by means of a free informatics tool, EPIDAT3.1. Treatment assignments will be conducted by an independent researcher at Primary Care Investigation Unit of Bizkaia (UIAPB) who will not interfere with the study.

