### Blinding

All patients will be blinded to the treatment to which they are allocated, thus peripheral blood is drawn even if they are assigned to the control group. All outcome assessors (orthopedists and radiologists) will be blinded, but the radiologists applying the treatment will not.

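### The baseline ultrasound falls after allocation, in the session of the unblinded treating radiologists, so the baseline of the secondary structural outcomes can be graded with the arm known

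*Protocol article*

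**What the plan says.** All references are to the protocol article.

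- **Order of events (Table 1).** The row "Eligibility screen" is marked at enrollment, 15 days before treatment. Allocation comes next, then the first intervention at time 0. Ultrasound is marked at time 0 and at 3, 6 and 12 months. It has no mark at enrollment.
- **Baseline scan (Procedures).** The section opens with the operators: "Interventions are performed by two radiologists with extensive clinical experience in musculoskeletal intervention procedures". It continues: "Prior to needling and administration of PRP or lidocaine, an exploratory echography is performed to identify clefts of hypoechogenicity". From this scan "baseline sonographic characteristics are recorded, as described in Table 2".
- **Blinding.** "All outcome assessors (orthopedists and radiologists) will be blinded, but the radiologists applying the treatment will not".
- **Grades (Table 2).** Echotexture and neovascularization are ordinal and judged by the reader. Full-thickness tear is grade 3 of the echotexture scale.
- **Outcomes.** Changes in echogenicity and vascularity at 3, 6 and 12 months are secondary outcomes. The Discussion names structural change in the tendon as one of three principal objectives.
- **Entry.** "Patients may not enter the study if any of the following apply: presence of full tendon tear". Primary care physicians and research nurses introduce the trial to patients and "refer them to an orthopedic investigator for screening and potential recruitment". No method for diagnosing a tear is named.
- **Analysis.** Efficacy is analysed by intention to treat.

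**The concern.** A change score has two ends, and both need protection from knowledge of the arm. Here the follow-up end is protected, because the assessing radiologists are blinded. The baseline end is not clearly protected: it comes after allocation, in a session run by people who know the arm.

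The grades are a matter of judgement, for example whether hypoechogenicity covers less or more than one-third of the tendon. A reader who knows that PRP is about to be given could, without intending it, grade the starting point differently from a reader who knows it is lidocaine. That would show as a difference in structural change with no difference between the tendons.

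A smaller, related gap is that a full tear is an entry exclusion, yet no imaging is scheduled at screening. A full tear could therefore first be seen after allocation, and the article has no rule for that case.

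**Working it through.** The plan attaches no figure to the sonographic outcomes; its 80 patients are sized on the DASH-E success rates. The check is therefore mainly a reading of the sections against each other, followed by simple arithmetic on how a baseline shift propagates.

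**1. Is the baseline scan after allocation?** Yes. Table 1 runs enrollment, allocation, time 0, and the first ultrasound mark is at time 0.

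**2. Who is in the room?** The Procedures section gives the session to two radiologists and puts the exploratory scan immediately before needling. The Blinding section says that those who apply the treatment are not blinded.

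**3. Is a blinded reader assigned to the baseline?** None is named. The Study population section asks patients to attend sonographic appointments at 3, 6 and 12 months only. The natural reading is that the treating radiologist grades the baseline and blinded radiologists grade follow-up. The article does not state this outright, nor when the operator learns the arm.

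**4. How does a shift at baseline reach the result?** Let the change be D = F − B, with F the follow-up grade and B the baseline grade. Suppose that knowing the arm makes the recorded baseline in one arm B + d on average, and leaves the other arm alone. Then:

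- recorded mean change in that arm = F − (B + d) = D − d;
- bias in the difference between arms = −d, that is, the whole shift.

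A plain difference between baseline and follow-up readers that is equal in both arms cancels. Only the arm-related part remains.

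**5. Size per patient.** Inputs: 40 patients per arm and about 20% loss (Sample size section), so 40 × 0.8 = 32 evaluable. A patient graded one level too high at baseline, with an unchanged tendon correctly graded later, counts as improved by one level.

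| Over-graded in one arm (assumed) | Apparent improvement rate, n = 40 | n = 32 | Shift in mean change, n = 40 |
|---|---|---|---|
| 1 | 1/40 = 2.5 points | 1/32 = 3.1 points | 0.025 level |
| 2 | 2/40 = 5.0 points | 2/32 = 6.3 points | 0.05 level |
| 4 | 4/40 = 10.0 points | 4/32 = 12.5 points | 0.10 level |

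The numbers of over-graded patients are illustrations; the documents give neither a rate nor a direction. The table concerns sonographic improvement, not DASH-E success.

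**6. Does it touch the primary outcome?** No. Success is a reduction of more than 25% in a patient-completed questionnaire and uses no sonogram.

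**The case against.** **The baseline reader is not named.** The Procedures section is in the passive, the Blinding section claims blinding for all outcome assessors including radiologists, and Table 1, which lists the time-0 ultrasound, is a table of outcome assessments. A blinded radiologist could be reading the baseline. This stands as far as it goes: unblinded grading is what the schedule permits and most naturally implies, not something the article asserts. It does not remove the point, because nothing assigns a blinded reader to a scan done in the treatment session.

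**Secondary outcomes only.** This stands and limits the severity.

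**The full-tear exclusion.** A reader might infer that this exclusion rests on the time-0 scan, so that an unblinded operator removes patients according to arm. The documents do not support that:

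- The eligibility screen comes before allocation and belongs to an orthopedic investigator. With no diagnostic method named, earlier or referral imaging is possible.
- Table 1 does not itemise eligibility tests. VAS has no mark at enrollment although pain above 3/10 is required for entry, and BMI has no row at all. A missing ultrasound mark does not show that tears go unchecked.
- The stated purpose of the time-0 scan is to look for hypoechoic clefts and vascular change. No section lets the radiologist exclude anyone or describes a withdrawal at that visit.
- Under the stated intention-to-treat analysis, such a patient stays in and the shift in the primary result is zero. Even if four future non-responders were dropped from one arm at the planned 65% (0.65 × 40 = 26 successes), the rate would become 26/(40 − 4) = 72.2%, a rise of 7.2 points against a planned gap of 93 − 65 = 28. That would need all four to be in one arm and all to be non-responders, identified six months in advance.

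**Block size.** The protocol states "Randomization will be performed in blocks of four", and a reader might add that the treating radiologists can predict allocations. They are not described as enrolling anyone, an independent researcher makes the assignments, and predicting the next allocation plays no part in grading a patient already allocated. It does not belong to this point.

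**Conclusion.** The point holds for the secondary structural outcomes. The baseline scan is scheduled after allocation, in a session run by unblinded radiologists, with no blinded reader assigned to it. If those radiologists grade it knowing the arm, any arm-related shift enters the change outcomes in full: 2.5 percentage points of apparent improvement for each patient over-graded by one level, at 40 per arm. Two assumptions carry this: that the treating radiologist is the baseline reader, and that the arm is known at the time of the scan. The documents make both likely but state neither. How large the bias would be cannot be derived from them.

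A full tear could first come to light at this scan, and the article does not say how such a patient is handled in the analysis beyond the general intention-to-treat statement. Arm-dependent exclusion is not established and is not part of the conclusion.

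The primary DASH-E comparison is unaffected. This should be fixed, because structural change is a declared principal objective and a pre-treatment grade cannot be retaken once treatment has been given. It does not threaten the trial's main result.

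**What to change.** Either of two changes to Table 1 and the Procedures section is enough:

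1. Perform and grade the baseline ultrasound at the screening visit, before allocation. No arm exists then, so no reader can know it.
2. Keep the scan at time 0, store the images, and have the Table 2 grades given by one of the blinded radiologists already planned for follow-up.

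In both cases, state who reads the baseline, and use the time-0 scan otherwise for guidance only. Add one sentence to the Statistical analysis section: every randomised patient stays in the intention-to-treat analysis, including any in whom a full tear is first seen after allocation. How such a patient is managed clinically is outside this point.

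Cost: no extra patients, outcomes or follow-up visits. Under option 1 the baseline may be up to 15 days before treatment. Under option 2 some blinded-reader time is needed, and the stored images must include the Doppler views on which neovascularity is graded.

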**Echotexture grading scale**	
0	Normal
1a	Hypoechogenicity in less than one-third of the tendon
1b	Hypoechogenicity in between one-third and two-thirds of the tendon
1c	Hypoechogenicity in more than two-thirds of the tendon
2	Partial-thickness tear
3	Full-thickness tear
**Neovascularization grading scale**	
0	No neovascularization
1	Neovessels on the tendon surface
2	1 or 2 intratendinous neovessels
3	3 or more intratendinous neovessels
**Tendon size (mm)**	
**Calcifications**	

### Needle tenotomy with PRP (or lidocaine)

Ultrasound-guided percutaneous needle tenotomy with PRP (or lidocaine) will be performed each alternate week for a total of two interventions. Blood will be drawn from all the patients’ unaffected arm and PRP prepared as described above. Using a single skin portal, local anesthetic (2 mL of 1% lidocaine HCl 10 mg/mL) will be injected into the subcutaneous tissue of the lateral or medial elbow using a 20 G needle. Once the needle is in place, the 5 mL Luer Lok syringe loaded with the treatment is attached. Multiple longitudinal and transversal penetrations of the tendon are performed, and 3 to 5 mL of PRP (or lidocaine) is delivered in multiple depots during needling fenestrations. The injected volume is adapted to the morphometric characteristics of each patient. The same protocol with lidocaine is performed in the control group.

### Study assessments

Study assessments will include the Spanish version [14] of the patient-reported outcome measure Disabilities of the Arm, Shoulder and Hand (DASH-E, Spanish version of the DASH, © Institute for Work & Health 2006), pain outcome as measured by the visual analogue scale (VAS) and changes in tendon structures and vascularity as assessed by Doppler sonography (Table 2).

DASH is a patient-filled questionnaire based on the patient’s subjective assessment of symptoms and abilities to perform activities of daily living on the last week. The range of available scores is 0 (best) to 100 (worst). The questionnaire will be administered to patients at the baseline and during their follow-up visits at 6 weeks, 3, 6, and 12 months.

The DASH disability/symptom score is calculated as follows: DASH score = ((sum of n responses/n)–1) × 25, where *n* is equal to the number of completed responses.

### Primary outcome measures

Successful treatment is defined as a reduction of >25% in the DASH-E score at 6 months post-treatment. The primary outcome measure is the percentage of patients that achieve a successful treatment. We will examine if the therapeutic success rates of the PRP and control groups are statistically different.

### Secondary outcome measures

Secondary outcomes include: percentage of patients that achieve a successful treatment at 6 weeks, 3, and 12 months; pain reduction as measured by changes in pain rating on a visual analogue scale (VAS) with respect to baseline; changes in echogenicity and vascularity as assessed by Doppler sonography at 3, 6, and 12 months.

Frequency, severity, intensity, and duration of adverse events will be recorded and the ratio of adverse events in both groups compared.

A summary of the study design is shown in Figure 1.

**Figure 1 F1:**
[figure not shown]
Study flow chart.

### Sample size

The minimum sample size required to achieve scientifically valid results is 80. This sample size provides an 80% potency to detect any significant difference between the success rates in both groups (*P*1 = 0.93 and *P*2 = 0.65) with a level of significance of 5%, being each arm formed by 40 patient. We have assumed that the relative improvement with the PRP intervention is 1.43, assuming that the differences between PRP and lidocaine would be similar to the differences reported with corticoids [8], and a patient loss of approximately 20%. However, this is a randomized study which will help to gain insights into feasibility of recruitment, and into the number of patients who become lost to follow-up.

### Randomization

Randomization will be performed in blocks of four, and equal allocation ratio will be achieved by means of a free informatics tool, EPIDAT3.1. Treatment assignments will be conducted by an independent researcher at Primary Care Investigation Unit of Bizkaia (UIAPB) who will not interfere with the study.

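### One fixed, published block size of four at a single centre with unblinded operators makes up to a third of allocations certain to anyone who tracks the earlier ones: a minor weakness in concealment, cheap to remove

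*Protocol article*

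**What the plan says.** All references are to the protocol article.

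- **List.** Under Randomization: "Randomization will be performed in blocks of four", and "equal allocation ratio will be achieved by means of a free informatics tool". No other block size and no stratification factor is mentioned.
- **Setting and size.** The abstract says: "This study is a single-center, randomized double-blind controlled trial". Study design adds: "A total of 80 patients will be randomly allocated into one of two groups". That makes 20 blocks of four.
- **Who sees the assignments.** Procedures: "Interventions are performed by two radiologists with extensive clinical experience in musculoskeletal intervention procedures". Blinding says that the outcome assessors are blinded, "but the radiologists applying the treatment will not".
- **Safeguards.** Randomization: "Treatment assignments will be conducted by an independent researcher at Primary Care Investigation Unit of Bizkaia (UIAPB) who will not interfere with the study". Study population gives screening and recruitment to an orthopedic investigator.
- **Order of events.** Table 1 puts the eligibility screen, consent and laboratory tests at −15 days, then allocation, then the first intervention and the first ultrasound at time 0. The exclusions in Study population include "presence of full tendon tear".

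**The concern.** In a 1:1 block of known size, the last assignments follow from the earlier ones. Here the size is published, and the two radiologists between them deliver every treatment knowingly. Together they can reconstruct the sequence as it unfolds. Central assignment protects the list itself, but it does not stop inference from treatments already given.

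Selection bias is what is at stake. If those who decide whether or when the next patient enters can foresee the arm, the groups may differ in prognosis from the start. The planned chi-squared comparison would not correct for that, and the Statistical analysis section plans adjustment only for imbalance seen in baseline data. With 40 patients per arm, one patient's outcome moves a success rate by 1/40 = 2.5 percentage points.

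**Working it through.** The article gives no figure for predictability, so there is none to reproduce. Inputs from the article are block size 4, ratio 1:1, 80 patients, two unblinded operators, screening at −15 days (Table 1) and four patients enrolled a month (Trial status).

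**1. Ceiling: all earlier allocations and the block boundaries are known.** A 2:2 block has 6 equally likely orders.

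| Position in block | Probability that it is certain | Best guess correct |
|---|---|---|
| 1 | 0 | 1/2 |
| 2 | 0 | 2/3 |
| 3 | 2/6 = 1/3 | 2/3 |
| 4 | 1 | 1 |

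Certain share: (0 + 0 + 1/3 + 1)/4 = 33.3%, or 80 × 1/3 = 26.7 patients on average. Best-guess rate: (1/2 + 2/3 + 2/3 + 1)/4 = 70.8%.

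**2. One operator alone.** Assume that each operator treats a random half of the patients and knows each patient's position in the block.

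- Position 3 is certain if the first two are alike (1/3) and both were seen (1/4): 1/12.
- Position 4 is certain if both of the first three patients who share an arm were seen: 1/4.
- Share: (1/12 + 1/4)/4 = 8.3%. Simulation gave 8.3%.

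**3. Delay between enrolment and treatment.** Assume that both operators pool what they see, that they learn an assignment only at treatment, and that selection happens at enrolment. Four patients a month is one about every 7.6 days (30.4/4).

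- With a 15-day delay and even spacing, only patients enrolled at least two places earlier are known. Position 4 is then certain when the first two are alike: (1/3)/4 = 8.3%. The best-guess rate is (1/2 + 1/2 + 2/3 + 2/3)/4 = 58%.
- With a 15-day delay and random arrivals, simulation gives about 7% certain and 56% guessed.
- With a 7-day delay, simulation gives about 16% certain with random arrivals. With even spacing the share stays at 33%, because 7 days is shorter than 7.6.

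**4. One leaked allocation.** With one assignment in a block known, three remain, two of them in the other arm. The best guess for any one of these rises from 1/2 to 2/3. Certainty needs at least two known assignments.

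**5. Other block schemes.** Fixed sizes were enumerated. Mixed sizes were simulated on 80-patient lists, with an observer who knows the possible sizes and the whole history.

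| Scheme | Certain | Best guess correct |
|---|---|---|
| Fixed 4 | 33.3% | 70.8% |
| Fixed 6 | 25.0% | 68.3% |
| Fixed 8 | 20.0% | 66.6% |
| Random 4 and 6 | about 6% | about 69% |
| Random 4, 6 and 8 | about 2% | about 68% |

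Two per cent of 80 is about 2 patients. Varying the size removes nearly all the certainty but little of the guessing advantage over 50%.

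**The case against.** The strongest reply is that those who can infer the sequence do not choose the patients. Recruitment belongs to an orthopedic investigator and assignment to an independent researcher at another unit. Nothing in the article says that the operators enrol, schedule or advise on entry. This stands, and it limits the point: bias needs information to pass from operators to recruiters. The article describes no barrier to that, but it does not say that it happens.

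A reader might infer three stronger things that the article does not support.

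- **That a third of allocations are simply known in advance.** This requires pooled knowledge, known block boundaries and no delay. It is an upper bound.
- **That the operators could use their pre-treatment scan to turn away a patient whose arm they foresee, by finding a full tear.** Table 1 and Procedures place that scan after allocation. An exclusion there would follow randomization, and block size would no longer matter. The timing is a reason to complete the imaging check before an allocation is released, not evidence that short blocks let operators select patients.
- **That one leaked assignment unblinds the assessors.** It only moves a neighbouring guess from 1/2 to 2/3. The primary outcome is also a questionnaire completed by blinded patients, so leakage to assessors would mainly touch the sonographic outcomes.

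Two further objections stand in part. A condensed article may omit stratification and the details of release, so a single list is a reading of what is printed. Mixed blocks also leave the best-guess rate at 68%, so they do not prevent selection that acts on probable guesses. Neither removes the point that the article itself fixes and discloses one small block size.

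**Conclusion.** The point holds as a minor weakness. For someone who knows the block boundaries and all earlier allocations, up to 33.3% of assignments (on average 27 of 80) are certain in advance. The share is nearer 8% for one operator treating a random half, or under a 15-day gap between enrolment and treatment at four patients a month.

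Concealment is weakened but not broken. The figures assume a single unstratified list, as the article reads. They measure predictability, not bias: no effect on the success-rate difference has been shown, and the sample size and significance level are untouched.

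**What to change.** Before the first patient is randomized, the independent unit should:

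1. generate the list with randomly varying block sizes, for example 4, 6 and 8;
2. withhold the sizes from all hospital staff, operators and recruiters included;
3. release each allocation only after all eligibility checks are complete, including the imaging check for a full tendon tear. Table 1 should show that check before allocation.

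The cost is one new list and a change to the order of checks. The largest end-of-list imbalance rises from 2 to 4 patients. The power loss is negligible: with 42 against 38, the information relative to 40 against 40 is about (42 × 38)/(40 × 40) = 1596/1600 = 99.75%, taking equal variances in the two arms.
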